**Outcome assessments pertaining to the secondary objectives:**

1. Compare differences in omental and subcutaneous immune cell composition levels before and after surgical lifestyle interventions.
2. Compare omental and subcutaneous immune cell composition levels to circulating levels after the intervention at the time of bariatric surgery.
3. Compare differences in mean plasma adiponectin, MCP-1, leptin and C-RP levels before and after the interventions with insulin sensitivity, and immune cells.
4. Compare differences in gut bacteria before and after the interventions and associate with changes in insulin sensitivity and immune cells.
5. Identify if changes in pre-operative insulin sensitivity, weight loss, inflammation (e.g. adiponectin, etc.) and immune cells predict changes in bariatric responses 1 month post-op.
6. Correlate at the time of bariatric surgery insulin sensitivity, immune cells, and weight loss with operating time.

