**4. What is your plan for primary variable analysis?**

***Analysis between weight loss, insulin sensitivity and immune health:***

Data will be analyzed using R (Vienna, Austria, 2011). A two-way repeated measures analysis of variance (ANOVA) will be used to assess time course differences (group x test) for **AIM 1** and **AIM 2**. A repeated measures ANOVA will also be used to assess differences in adipose cell depot among groups (**AIM 3**). Bonferonni post-hoc analysis will be used to determine group differences and paired t-tests will be used to assess within treatment effects. Linear regression analyses will be used to identify relationships between respective variables. A *P*<0.05 will be considered statistically significant. Data will be expressed as mean ± SEM.

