**Vascular tests:**

*Blood pressure:*

- - The subject’s blood pressure will be taken: before the MMTT and every hour afterwards (at about the same time their blood is being drawn). This test takes about 5 minutes.
- **Augmentation Index (AI)** This measures the pulse wave of the vessel and its characteristics, which is an assessment of the stiffness of the aorta. Researchers will use an aplanation tonometer from SphygmoCor. This is done by placing a blood pressure cuff around the subject’s arm and measuring several waveforms. This will take 2-5 minutes and is comparable to routine blood pressure readings.
- **Pulse Wave Velocity (PWV)** This measures the time difference between the pulse wave at the carotid artery and the pulse wave at the femoral artery. This will allow researchers to assess the “stiffness” of the larger vessels. The shorter the time difference, the stiffer or less elastic the vessels are. Researchers will use the same device as described above. Specifically, a probe that looks like a “fat” pen will be placed over the carotid artery at the neck and a blood pressure cuff will be placed around the upper leg. Researchers measure the time between the heartbeat and when the probe picks up the pulse wave with the tonometer. This will take about 10-15 minutes.
- **Brachial Artery Flow Mediated Dilation (FMD)** Brachial artery diameter is measured using ultrasound at baseline and then after five minutes of forearm ischemia. The subject will supine in bed.  The first measurement is taken (velocity and diameter) and then a blood pressure cuff placed around the forearm is pumped to 200 mm/Hg and held for 5 minutes.  The brachial artery will be observed with ultrasound as the BP cuff is deflated and for 2 minutes post cuff deflation.  This will take approximately 10 minutes. We will perform this procedure just before the beverage, and then again at 1, 2, and 3 hours after the drink.

**Adipose Biopsy***:*

- Adipose biopsy samples will be taken during MMTT/OGTT (Optional). The biopsy involves removal of a very small piece of fat tissue beneath the subject’s skin (referred to as subcutaneous fat) and is about the amount of a pencil eraser. This is performed by way of a needle inserted into your belly area near your navel (belly-button) through a quarter inch skin incision. Local anesthesia will be used to numb the area where the incision will be made. Fat biopsies will be performed on alternate sides of the stomach.

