***Phase 6: Bariatric Surgery (if applicable)***

Subjects undergo bariatric surgery within 1 week, although **3-4 days** following the phase 5 testing will be targeted. Following your surgery, the research team will examine certain details from the procedure. Specifically, the research team will look at the bariatric surgery operation time and any surgery complications that may occur. A fat biopsy will be collected during the time of surgery and within 3-4 days of the intervention assignment.

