**2b. Explain compensation to be given.**

Bariatric subjects will be compensated per completion of phases:

Completion of Phase 1-3: $**100 (or $150 if pre-test fat biopsy performed)**

Completion of Phase 4-5: $**250**

Completion of Phase 7: $**100**

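### In the surgical arms, before/after change in subcutaneous immune cells compares an optional needle biopsy with a sample taken at operation, so a paired within-arm test cannot be credited to the intervention

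*Protocol*

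**What the plan says.** Secondary outcome 1 in the Protocol is to "Compare differences in omental and subcutaneous immune cell composition levels before and after surgical lifestyle interventions". Statistical Considerations, item 4, plans paired t-tests for effects within a treatment, and item 5 carries the same approach over to secondary variables. For tissue, item 4 adds: "A repeated measures ANOVA will also be used to assess differences in adipose cell depot among groups", tied to AIM 3.

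The first sample is described under Adipose Biopsy: "Adipose biopsy samples will be taken during MMTT/OGTT (Optional"). It is the "removal of a very small piece of fat tissue beneath the subject’s skin (referred to as subcutaneous fat"), and "This is performed by way of a needle inserted into your belly area near your navel". The payment section confirms that it can be declined: for Phases 1-3 a bariatric subject receives $"100 (or $150 if pre-test fat biopsy performed").

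The second sample comes from Phase 6: "A fat biopsy will be collected during the time of surgery". The visit schedule for bariatric patients marks a biopsy at Pre-Test Visit 3 and at surgery, and leaves the post-intervention visit blank. The specimen list in Specimen Banking, item 4, likewise names tissue at pre-intervention testing and at surgery. Non-bariatric subjects have a biopsy marked at both the pre-test and the post-intervention visit, alongside the OGTT.

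**The concern.** In both surgical arms, time and sampling setting change together. The earlier sample is an outpatient needle biopsy near the navel under local anaesthetic, during a mixed-meal test. The later one is taken in the operating room. Anything in the setting that alters measured immune cell composition appears as change over time, and the planned paired t-test would report it as an effect of exercise or of standard care.

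A paired test also needs both samples, so its population is those who agreed to an optional biopsy, not those who were operated on.

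At stake is the interpretation of one secondary outcome in one cohort. It still matters, because item 3 of Statistical Considerations says the data are meant to supply power calculations for later studies and grant proposals. A sampling artefact recorded as a treatment effect would carry forward.

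**Working it through.** **1. The plan's own figures.** Item 3 gives delta 2 with SD 1.2 (5 subjects) and a change from 2.5 to 4.9 with SD 1.5 (6 subjects), at 80% power and alpha 0.05, then 8 per surgical group after 20% dropout. Take the SD as the SD of change and use a two-sided paired t-test, where power comes from the noncentral t with n - 1 degrees of freedom and noncentrality (delta/SD) x sqrt(n):
- 2/1.2 = 1.667. Power is 79.3% at n = 5 and 89.9% at n = 6, so 6 by strict count; the plan's 5 falls just short of 80%.
- 2.4/1.5 = 1.6, which needs n = 6.
- 6/(1 - 0.2) = 7.5, rounded up to 8 per group.

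The figures reproduce closely. They concern insulin resistance; no figure is given for tissue.

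**2. The samples side by side.**

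| | Before | After |
|---|---|---|
| Bariatric | Optional needle biopsy, subcutaneous, during MMTT | At operation |
| Non-bariatric | Optional needle biopsy, subcutaneous, during OGTT | The same |

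Only the non-bariatric cohort has like-for-like samples. In the bariatric cohort the before/after question can concern only the subcutaneous depot, because the first biopsy takes no omental tissue.

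**3. Who can enter the paired test.** Human Participants, item 2, expects 12 surgical completers, about 6 per arm. Uptake of the first biopsy is not stated. Assuming 50-80%:
- 12 x 0.5 = 6 and 12 x 0.8 = 9.6, so roughly 6 to 10 subjects, or 3 to 5 per arm.
- At the plan's standardised effect of 1.667, paired power is 37% with 3 pairs, 61% with 4 and 79% with 5, against 90% with 6.

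**4. What a setting shift does within an arm.** Write a subject's observed change as t + m + error, where t is the arm's true change and m the shift due to setting. The paired test examines t + m and cannot separate them. With t = 0, 6 pairs and m assumed in SDs of change (20,000 simulated trials):

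| m (SD) | Within-arm test significant | Ex versus SC difference in change significant |
|---|---|---|
| 0 | 5% | 5% |
| 0.5 | 17% | 5% |
| 1.0 | 50% | 5% |
| 1.5 | 83% | 5% |

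The exact noncentral-t value for m = 1.0 is 50.7%, which agrees with the simulation. With fewer pairs the same 1.0 SD shift is flagged in 18%, 29% and 40% of trials at 3, 4 and 5 pairs. Lower uptake therefore reduces false positives only by weakening the test.

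**5. Between arms.** With the same m in both arms, the difference in change is (t_Ex + m) - (t_SC + m) = t_Ex - t_SC. The shift drops out, as the last column shows.

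**The case against.** Several points on the other side stand.

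- **The arm comparison.** A reader might infer that exercise versus standard care is confounded too. The documents do not support that: both surgical arms follow one sampling scheme, so a common additive shift cancels. Only a shift that differed by arm would remain, and nothing in the protocol suggests one.
- **The AIM 3 ANOVA.** A reader might also infer that this analysis needs the baseline biopsy and shrinks to those who accepted it. Primary objective 3 places the tissue at surgery or at post-intervention testing, and item 4 reserves time-course language for AIMs 1 and 2. The natural reading is depot by group at surgery, for which no first biopsy is needed. Secondary outcome 2 also uses at-surgery tissue only.
- **Technique at surgery.** It is not described, nor is the patient's metabolic state at operation. The change of setting is documented; a change of method is only inferred.
- **Phase 5.** It says the testing visits are repeated, which could be taken to include a second needle biopsy, and the biopsy text mentions alternating sides. The bariatric schedule, specimen list and payment terms name no such biopsy. If one is intended, a like-for-like comparison exists and the confounding falls away.
- **Counts.** Uptake is assumed. The 12 are study completers, and completion includes post-surgery testing, so the number operated on may differ.
- **Non-bariatric cohort.** Its biopsies are optional at both visits, so self-selection is not confined to the surgical arms; the change of setting is.

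**Conclusion.** The point holds in a limited form. Under the bariatric visit schedule as written, secondary outcome 1 with the paired within-treatment tests cannot separate the intervention from the change of sampling setting for subcutaneous tissue, and it can use only subjects who accepted the first biopsy.

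Its size cannot be fixed from the protocol. About 6 to 10 subjects with both samples rests on an assumed uptake of 50-80% of 12 completers. A false-positive rate of 17% to 83% rests on an assumed setting shift of 0.5 to 1.5 SD of change with 6 pairs per arm.

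Neither the exercise versus standard-care difference in change nor the AIM 3 analysis is invalidated. The difference in change is, however, limited to subjects with both samples. The matter is worth correcting before analysis because the correction is cheap and the within-arm test as planned would mislead.

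**What to change.** In secondary outcome 1 and in Statistical Considerations, item 4, for the bariatric cohort:

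1. State that within-arm before/after subcutaneous change is descriptive only, with no paired test credited to the intervention.
2. Compare exercise with standard care by depot on the at-surgery samples of all operated subjects.
3. Keep the exercise versus standard-care difference in subcutaneous change, among those with both samples, as a supportive analysis, and report how many accepted the first biopsy in each arm.
4. Reconcile Phase 5, which repeats the testing visits, with the bariatric schedule, which marks no post-intervention biopsy.

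The non-bariatric before/after comparison can stay, with the number of paired samples reported.

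The change is to wording only and adds no procedure or visit. The real cost is that the at-surgery comparison has no adjustment for baseline tissue, in arms formed by matching and not by randomisation. That is why the difference in change is retained as support.

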**Outcome assessments pertaining to the primary objective:**

- 1. Assess the absolute mean difference in the 3-hr postprandial glucose AUC between the 2 different conditions undergoing bariatric surgery and the 2 different groups not undergoing bariatric surgery.
  2. Assess the absolute mean difference in the 3-hr postprandial insulin AUC between the 2 different groups undergoing bariatric surgery and the 2 different groups not undergoing bariatric surgery.
  3. Compare the postprandial insulin sensitivity across conditions (as measured by the insulin sensitivity index- ISI; a calculated value based on the glucose/insulin values obtained from the MMTT or OGTT)
  4. Compare the mean change in body fat between groups.
  5. Compare the mean change in body weight between groups.
  6. Assess the change in cardiorespiratory fitness between groups.
  7. Determine and compare the immunophenotype from blood between groups.
  8. Relate the insulin sensitivity responses to the immunophenotyping from blood via correlations.
  9. Relate the pulse wave velocity responses to the insulin sensitivity and immunophenotyping under each condition by calculating a 3-hour pulse wave velocity AUC.
  10. Relate the augmentation index responses to the insulin sensitivity and immunophenotyping under each condition by calculating a 3-hour pulse wave velocity AUC.

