**3. Provide a justification for the sample size used in this protocol.**

*No prior work has studied adipose immune cell health in bariatric patients before or after surgery or in response to Ex+CR.* As a result, data collected in the proposed study will serve as preliminary work to determine power analysis for future studies and NIH proposed grants.

Nonetheless, the appropriate sample size required for significant differences following Ex+CR testing and surgery was, however, determined from our preliminary work (6, 11) on insulin resistance given it’s direct relation to adiposity-related immunity. A delta of 2 (Pre = 3.5 vs. Post = 5.5 surgery), SD of 1.2 with 80% power and an alpha of 0.05 indicates that **5** subjects are needed to show insulin resistance differences post-surgery, which is consistent with Ex+CR reducing insulin resistance in **6** people (Pre = 2.5 vs. Post = 4.9), SD of 1.5 at 80% power. **Thus, assuming a 20% dropout rate, 8 are required per group** **undergoing bariatric surgery.**

In contrast, subjects undergoing diet+exercise vs. diet intervention will require more subjects. This is based on an diet+exercise published study (43) on insulin resistance and energy deficit (i.e. weight loss). A delta of 3.1kg (Exercise = 3.7kg vs. Exercise+diet = 6.8kg), SD of 3.1kg with 80% power and an alpha of 0.05 indicates that **10** subjects are needed to show energy deficit differences. **Thus, assuming a 20% dropout rate, 14 will be required per group** **NOT undergoing bariatric surgery.**

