**5. What is your plan for secondary variable analysis?**

The same statistical approach to primary variable analysis will be conducted.

Bivariate regression analysis to understand the relationship between blood and urine MPs to inform future studies which tissue to collect from. Currently, it is not understood how MPs collected in the blood relate to MPs collected in the urine.

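### Secondary outcome 5 relates two changes that share a visit whenever the same measure is on both sides, and the group contrast in the randomised diet arms gives up precision by omitting the baseline value

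*Protocol*

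**What the plan says.** For the group comparisons, Protocol, Statistical Considerations item 4 states: "A two-way repeated measures analysis of variance (ANOVA) will be used to assess time course differences (group x test) for" aims 1 and 2. Bonferroni post-hoc tests and paired t-tests are added, and no baseline covariate is named. Item 2 describes some of the outcomes as changes, for example "Compare the mean change in body weight between groups".

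For associations, item 4 says "Linear regression analyses will be used to identify relationships between respective variables", and P<0.05 "will be considered statistically significant". Item 5 carries this over to secondary variables: "The same statistical approach to primary variable analysis will be conducted".

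Secondary outcome 5 in item 2 is to "Identify if changes in pre-operative insulin sensitivity, weight loss, inflammation (e.g. adiponectin, etc.) and immune cells predict changes in bariatric responses 1 month post-op". The predictors are listed. The response is given only in general terms, and the starting visit for the post-operative change is not stated.

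The bariatric visit schedule repeats the meal test and the body-fat measurement before the intervention (Y0), after it (Y1) and after surgery (Y2). The same measure is therefore available for both changes.

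**The concern.** Two separate points arise.

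**(a) Group contrasts.** With one test before and one after, the group x test interaction is algebraically the comparison of mean change between groups. That is valid, but it does not use the correlation between baseline and follow-up. In so small a study the lost precision may matter.

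**(b) Secondary outcome 5.** For a single measure, the pre-operative change is Y1 - Y0. If the post-operative change is Y2 - Y1, the Y1 value enters both sides with opposite sign. If it is Y2 - Y0, the Y0 value is shared and the total change contains the pre-operative change as a part. A correlation then arises without any effect of pre-operative improvement on surgical response, and the usual test against zero reports it as a finding. Its sign depends on a reference visit that the protocol leaves open. With the baseline reference the artefact is positive, the direction in which larger pre-operative change seems to predict larger response.

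**Working it through.** **Inputs from the Protocol.** Human Participants item 2 expects 12 bariatric completers and 24 non-bariatric completers (about 12 per arm). Statistical Considerations item 3 gives a weight-loss difference of 3.1 kg with SD 3.1 kg, i.e. 1 SD, and a stated n of 10. Alpha is 0.05, taken as two-sided. The correlation between visits (rho) is not given, so it is an assumed range.

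**The plan's own figure.** A one-sample or paired t-test with delta/SD = 1, 80% power and alpha 0.05 gives n = 10 (power 0.803), which reproduces the stated 10. A two-sample t-test with the same inputs needs 17 per arm. The contrast of interest is between arms, so the two-sample form is used below.

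**(a) Change score against ANCOVA, randomised diet arms.** With equal variance s² at both tests:

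- Var(change) = 2(1 - rho)s²
- Var(follow-up given baseline) = (1 - rho²)s²
- Ratio = (1 + rho)/2

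Take the stated SD as the SD of change. At 12 per arm the noncentrality is 1 x sqrt(12/2) = 2.449 on 22 df, and power is 0.649. ANCOVA divides the noncentrality by the square root of the ratio and uses 21 df:

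| rho (assumed) | ratio | noncentrality | power |
|---|---|---|---|
| 0.5 | 0.75 | 2.828 | 0.769 |
| 0.7 | 0.85 | 2.657 | 0.717 |
| 0.9 | 0.95 | 2.513 | 0.669 |
| 0.99 | 0.995 | 2.456 | 0.649 |

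**(b) Change on change, same measure, no relation beyond the correlation between visits.**

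*Equal variances and equal correlations:*
- Cov(Y1 - Y0, Y2 - Y1) = -(1 - rho)s² and each variance is 2(1 - rho)s², so r = -0.5 whatever rho is.
- Cov(Y1 - Y0, Y2 - Y0) = +(1 - rho)s², so r = +0.5.

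*Correlation decaying with distance, AR(1), so that corr(Y0, Y2) = rho²:*
- Post-intervention reference: r = -(1 - rho)/2 = -0.25, -0.15, -0.05 at rho 0.5, 0.7, 0.9.
- Baseline reference: r = sqrt(1 + rho)/2 = 0.61, 0.65, 0.69.

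*Larger post-operative SD, equal correlations of 0.7:* the size falls to 0.36 when that SD is 1.5 times the others and to 0.26 when it is twice the others.

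Simulated rejection rates at nominal 5%, n = 12:

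| Structure | rho | Y2 - Y1 on Y1 - Y0 | Y2 - Y0 on Y1 - Y0 | Y2 on Y1 - Y0, adjusted for Y1 |
|---|---|---|---|---|
| Equal correlations | 0.5 | 40% | 40% | 17% |
| Equal correlations | 0.7 | 40% | 40% | 25% |
| Equal correlations | 0.9 | 40% | 40% | 33% |
| AR(1) | 0.5 | 12% | 60% | 5% |
| AR(1) | 0.7 | 7% | 69% | 5% |
| AR(1) | 0.9 | 5% | 76% | 5% |

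The last column shows the limit of the obvious remedy. Regressing Y2 on Y1 - Y0 with Y1 as covariate is the same test as Y2 on Y0 given Y1. Under equal correlations its partial correlation is -rho/(1 + rho), i.e. -0.33, -0.41 and -0.47 at rho 0.5, 0.7 and 0.9. Adjusting instead for the mean of Y0 and Y1 restores 5% under equal correlations but gives 13% to 26% under AR(1). No single adjustment is right under both structures.

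**The case against.** *Group x test ANOVA is a legitimate analysis, and covariates are often left to a statistical analysis plan.* This stands. In randomised arms regression to the mean is the same in expectation on both sides, so change scores are unbiased there. Point (a) is a gain forgone, not an error, and it vanishes for very stable measures.

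*ANCOVA is least secure in the bariatric cohort.* This also stands. Those arms are matched, not randomised, and ANCOVA and change scores can then estimate different quantities. The precision case is also weak there. Using delta 2 and SD 1.2 from item 3 purely for illustration (SD taken as that of change), 6 per arm gives power 0.740 for the change score. ANCOVA with baseline and BMI as covariates gives 0.783, 0.737 and 0.726 at rho 0.7, 0.9 and 0.95.

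*The coupling is conditional.* A reader might infer that the plan builds in a spurious correlation of 0.5. The protocol does not support that. It does not say that predictor and response are the same measure, and different measures share no such term. The value 0.5 also needs equal variances and equal correlations.

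*The stakes are limited.* A reader might infer that the central hypothesis itself will be judged by a test with a 40% error rate. Outcome 5 is close to that hypothesis in content. It is, however, one of six secondary outcomes, none of the three primary objectives is this regression, and item 3 presents the data as preliminary for future power calculations.

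*The ANOVA need not include the post-surgery test.* The protocol gives no number of test levels, and item 2 speaks of measurement before and after the interventions. That the interaction mixes in the 1-month test is a possible reading only, which one sentence would close.

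**Conclusion.** Both points hold in limited form.

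(a) In the randomised diet arms, omitting the baseline value costs roughly 12, 7 or 2 points of power at rho 0.5, 0.7 or 0.9, for a 1-SD effect with 12 per arm, and nothing at rho near 1. This assumes equal variances and the stated SD as the SD of change. It also takes those arms as randomised, as Study Design and the Phase 4 text say; Statistical Considerations item 1 answers that no randomisation is involved, and the two should be reconciled.

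(b) For any measure used on both sides of secondary outcome 5, zero is the wrong null. With 12 completers the nominal 5% test rejects about 40% of the time under equal variances and correlations. Under AR(1) it rejects about 60% to 76% with the baseline reference and 5% to 12% with the post-intervention reference. What the protocol establishes is that the response and reference visit are undefined; the size of the artefact depends on a covariance it does not give. The point is worth correcting before analysis but concerns a secondary outcome.

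**What to change.** 1. **Randomised non-bariatric arms:** replace the group x test interaction with ANCOVA of the post-intervention value on group, adjusted for the baseline value of the same outcome.
2. **Matched bariatric arms:** base the pre-surgery contrast on the two pre-surgery tests only and analyse the 1-month test separately. Report baseline adjustment as a sensitivity analysis.
3. **Secondary outcome 5:** name each response and the visit from which its change is measured. Do not test change on change against zero when the measure is the same. Model the 1-month value with the earlier values as covariates, and show how the result moves with the assumed covariance, for instance by comparing adjustment for the post-intervention value with adjustment for the mean of the two pre-operative values. State that adjustment for the post-intervention value alone reduces the bias but does not remove it under equal correlations.

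The cost is wording, one degree of freedom per added covariate, and a short sensitivity table. All the measurements are already scheduled.
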